### Demographic measures

2.19

Demographic data table, including; age, gender, height, weight, race, religion, marital status, smoking status, previous back pain episodes, previous back pain treatment methods, current treatment methods, and current exercise activities, will be completed during the assessment.

### Data management and quality control

2.20

The study used paper case report form to collect data that had been approved by the Ethics committee. All the original paper data will be managed by specialized personnel to ensure the safety of patient data. At the end of the study, all documents will be safely stored for 5 years. All practitioners and researchers have been trained in good clinical practice. In order to improve the quality of Baduanjin, patients will be trained by professional teachers with more than 5 years of experience.

### Statistics

2.21

All data are statistically analyzed using Statistical Product and Service Solutions (SPSS©), version 20.0 (IBM Corp., Armonk, NY, USA). Continuous variables will be mapped by the mean and its SE (normal distribution) or median and IQR (non-normal distribution). Categorical variables will be delineated as a frequency or percentage. The baseline characteristics between the comparison groups will be compared using the *t* -test or Mann-Whitney *U* test for continuous variables, while Pearson χ^2^ or Fisher exact test will be employed to compare categorical variables. The analysis of primary or secondary results will be established with the intent to treat principle, and missing data will be interpolated using multiple imputation methods. Student's *t* test or Mann-Whitney *U* test will be used to analyze the difference between the intervention group and the control group at each time period (8 weeks after the intervention, 16 weeks, and 24 weeks or 4 weeks of follow-up). In the safety analysis, the total adverse event rate and adverse event rate associated with Baduanjin were tested by Pearson χ^2^ or Fisher's exact test.

Primary analysis: treatment efficacy. The statistical analysis of primary and secondary results will be based on treatment principles. The effect of the intervention on pain distress, pain intensity, function, disability, and overall sensory effects will be determined using a linear mixed model (random intercept and fixed coefficient), which includes treatment, time, and time interaction. The treatment coefficient of time interaction provides an estimate of the effect of Baduanjin intervention. The magnitude of the treatment effect will be calculated for each follow-up time point. If there is a statistically significant treatment effect at any point in time, we will also calculate the number of treatments (NNT) required to achieve pain recovery.

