### Subject withdrawal criteria

2.5

1.Violate the inclusion criteria or meet the exclusion criteria;2.Serious adverse events hindered the continuation of the trial;3.Withdraw the consent of the subject or legal representative;4.Do not receive the entire course of treatment continuously;5.The investigator or subject violates the clinical trial protocol;6.Use of drugs or treatments that may affect the results of clinical trials without the permission of the researcher;7.The researcher believes that the progress is inappropriate.

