### Sample size calculation

2.7

Perform sample size calculations to determine the appropriate number of participants. The main outcome will be the change of VAS score between the intervention group and the control group from before the intervention to the end of the last intervention. As far as we know, a previous clinical trial evaluated the effects of Baduanjin and conventional rehabilitation intervention for 8 weeks.^[28]^ The change of VAS score after treatment group (8^th^ week) was 2.37 ± 1.7 in the treatment group and 3.70 ± 1.39 in the control group. The following indicators will be considered: α = 0.05, statistical power of 95%, and follow-up loss of up to 20%. We use G∗POWER 3.1.9.7 (http://stats.idre.ucla.edu/other/gpower/) to calculate that the sample size of this study is 45 patients per group. Therefore, a total of 90 participants are required.

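### Withdrawal for an incomplete course, combined with multiple imputation, can let the week-24 estimate exceed the declared intention-to-treat effect; sections 2.5 and 2.21 need reconciling

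*Protocol article*

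**What the plan says.** All references are to the protocol article.

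- **Statistics (2.21), principle:** "The analysis of primary or secondary results will be established with the intent to treat principle".
- **Statistics (2.21), missing outcomes:** "missing data will be interpolated using multiple imputation methods". The imputation model, its variables and its missingness assumption are not described.
- **Statistics (2.21), models:** group comparisons at each visit by t-test or Mann-Whitney test, and efficacy by a "linear mixed model (random intercept and fixed coefficient), which includes treatment, time, and time interaction".
- **Subject withdrawal criteria (2.5), item 4:** "Do not receive the entire course of treatment continuously". Item 6 also withdraws participants for unpermitted drugs or treatments.
- **Sample size calculation (2.7):** allows for "follow-up loss of up to 20" per cent.
- **Visits and records:** outcomes are scheduled at baseline, at weeks 8, 16 and 24, and four weeks later (2.2). Training days are recorded (2.15).
- **Primary endpoint (2.16.1):** change in patient-marked VAS from baseline to week 24.

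No section says whether a withdrawn participant is still assessed at the remaining visits.

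**The concern.** Intention to treat asks what happens to everyone assigned to Baduanjin, including those who stop. Under item 4 of section 2.5, stopping is itself a ground for withdrawal. If withdrawal ends measurement, the missing week-24 values in that arm come largely from people who stopped, and the observed values largely from people who continued.

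An imputation that assumes missing at random within arm then predicts the stoppers from the continuers. The result leans towards the effect had everyone continued, which is a different quantity from the one declared. A mixed model fitted to the incomplete data relies on the same kind of assumption, and t-tests on imputed data inherit it. The analyses named in section 2.21 would therefore agree with one another without testing it. Participants cannot be blinded (2.9) and the outcome is self-reported, so the primary conclusion could rest partly on this assumption.

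**Working it through.** **Inputs.** From section 2.7: means 2.37 (SD 1.7) and 3.70 (SD 1.39), two-sided α 0.05 (sidedness assumed), power 95%, loss up to 20%, 45 per group. The difference is 3.70 − 2.37 = 1.33, taken here as a benefit of Baduanjin. Pooled SD = √((1.7² + 1.39²)/2) = 1.553.

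**The plan's own figure.** n = 2 × (1.960 + 1.645)² × 1.553² / 1.33² = 35.4, so 36 per arm, and 36/0.8 = 45. The stated 45 per group reproduces, so 20% loss is built into the design.

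**Possible size.** Let D = 1.33 be the effect in those who continue, p the share of the Baduanjin arm lost, and f the share of benefit that lost patients keep. The documents do not give p by arm or f, so both are assumptions. Suppose the imputation has no off-training information and control loss is uninformative. Then:

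- intention-to-treat effect = D × [(1 − p) + p × f]
- imputation returns about D
- overstatement = D / (intention-to-treat effect) − 1

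| p | f | Intention-to-treat effect | Excess | Overstatement |
|---|---|---|---|---|
| 20% | 0 | 1.33 × 0.8 = 1.06 | 0.27 | 25% |
| 20% | 0.5 | 1.33 × 0.9 = 1.20 | 0.13 | 11% |
| 20% | 1 | 1.33 | 0 | 0% |
| 10% | 0 | 1.33 × 0.9 = 1.20 | 0.13 | 11% |
| 10% | 0.5 | 1.33 × 0.95 = 1.26 | 0.07 | 5% |

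The percentages depend only on p and f, not on D or the VAS unit.

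**Interval coverage in the extreme row only (p = 20%, f = 0).** SE = 1.553 × √(2/36) = 0.366. Bias/SE = 0.266/0.366 = 0.73. A nominal 95% interval then covers the intention-to-treat value about 89% of the time.

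**With week-16 pain in the model.** Suppose patients had already stopped and lost all benefit by week 16, were measured then, and the week-16 to week-24 correlation is 0.6 (assumed). The imputation recovers 0.6 of the shortfall. The remaining excess is 0.2 × (1 − 0.6) × 1.33 = 0.106, and 0.106/1.064 = 10%. A simulation of this case gave 1.18 against 1.07, also about 10%.

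**With informative control loss.** In general, excess = p(Baduanjin) × shortfall(Baduanjin) − p(control) × shortfall(control), where shortfall is how much worse lost patients fare than those still measured in the same arm. With 20% loss and a shortfall of 1.33 in both arms, the excess is 0.266 − 0.266 = 0. Simulation agreed (true 1.335, imputed 1.332).

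**The case against.** The strongest reply is that the article describes no particular imputation model. Missing at random within arm is inferred, and the model could use earlier pain scores or attendance. Imputation models and sensitivity analyses are commonly left to a statistical analysis plan or full protocol, which are not shown. That stands: their absence alone is no finding. What remains is that two rules the article does state, withdrawal for an incomplete course and intention to treat, leave open whether the data intention to treat needs will be collected.

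Stronger readings are tempting, and the documents do not support them:

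- **That the effect is overstated as a fact.** No section gives loss by arm, reasons for loss or outcomes after stopping. The 25% needs the maximum planned loss, no benefit kept and no help from interim visits.
- **That the bias is one-sided because controls have no training to stop.** Controls can be withdrawn for unpermitted treatments (2.5). The Discussion describes removing patients whose daily activity changed markedly, in a remark about control-arm activity. Such loss could offset the bias or add to it.
- **That adverse events drive it.** "Serious adverse events hindered the continuation of the trial" is one withdrawal criterion, but nothing suggests such events would approach 20%. Item 4 is the relevant rule.
- **That the second statement of principle, "The statistical analysis of primary and secondary results will be based on treatment principles", announces an on-treatment analysis.** It reads as a garbled repetition of intention to treat, so no weight is placed on it.

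The 1.33 is also a weak benchmark. The Discussion concedes that its source trial lasted 8 weeks and had a different control group. This affects the absolute figures, not the percentages.

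**Conclusion.** The point holds conditionally. If withdrawn participants are not measured, and if imputation assumes missing at random within arm, the week-24 estimate can exceed the intention-to-treat effect that section 2.21 declares. At an assumed 20% loss the overstatement is 0% to 25%, or 0 to 0.27 on the planning difference of 1.33. It is about 10% in the no-benefit-kept case when week-16 pain after stopping informs the model (assumed correlation 0.6). These figures take control-arm loss as uninformative, and the net direction is not certain without that. The issue should be settled before analysis. It is a matter of reconciling sections 2.5 and 2.21, not evidence that the trial's result will be wrong.

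**What to change.** 1. **Reconcile 2.5 with 2.21.** State that stopping training does not end outcome collection at the visits already scheduled, and that any VAS measured after stopping is analysed as observed. This concerns data collection only; the grounds for stopping treatment are not at issue.
2. **In 2.21, keep multiple imputation as the main analysis**, and name the week-8 and week-16 VAS as variables in the model.
3. **Add one pre-specified sensitivity analysis of the primary endpoint.** Baduanjin patients who stopped training (identified from the attendance records) and lack a week-24 VAS are imputed from the control-arm model given their own earlier values.
4. **Report both estimates with confidence intervals**, and call the result robust only if the sensitivity interval also excludes zero.

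The control-based analysis is one plausible assumption among several (delta adjustment and tipping-point analysis are others) and does not recover the truth. Because it conditions on earlier values, it carries forward part of any benefit seen before stopping. That is why it belongs beside the main analysis and does not replace it.

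The cost is a paragraph of text and a second run of the imputation, with no extra patients and no visits beyond those scheduled. The downside is a second, probably smaller and less favourable estimate. As a rough guide, if the effect were 1.06, a two-sided t-test with 36 per arm would have about 82% power, against about 95% at 1.33.

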### Research design

2.2

This study is a randomized, controlled clinical trials, will conform to the conditions of 90 participants according to the proportion of 1:1 were randomly divided into intervention group (Baduanjin group) and control group (not exercise training group). All the members of the intervention group received Baduanjin training 3 times a week for 24 weeks. All cases in the control group did not receive any exercise training for 24 weeks. Primary and secondary outcomes will be measured at baseline, 8, 16 and 24 weeks after intervention, and the next 4 weeks. The research design flowchart is shown (Fig. 1). The research protocol was described in accordance with “ SPIRIT 2013 statement: defining standard protocol items for clinical trials ”.^[29]^

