### Control group

2.13

Participants in the control group did not receive any special sports training. These participants will be required to maintain their original lifestyle.

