### Assess safety

2.18

Each examination will be a physical examination, and vital signs and adverse events will be checked. To check the safety of Baduanjin, blood pressure, heart rate, blood tests and nervous system checks will be performed during the first and fourth data collection. Any adverse events during the clinical trial will be documented and evaluated in the case report form. The incidence of adverse events will be calculated. Adverse events associated with the intervention will be monitored and appropriately addressed.

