Our research has many advantages. First of all, All Baduanjin are personally guided by professional teachers of more than 5 years to improve the quality of experimental data. Second, we will not only assess pain intensity, but also clinical relevance, quality of life, level of disability, and overall assessment. Third, the intervention effect of each recorded time point was analyzed statistically, build a hybrid linear model, to provide basic data for the treatment course and training frequency of Baduanjin. Fourth, economic evaluation is included for the first time to provide data for the urban benefit of Baduanjin. Fifth, safety index evaluation is included for the first time to verify the safety of Baduanjin training. However, our research also has some limitations. First of all, our sample size calculation may be overestimated. According to previous study, the duration of treatment was only 8 weeks, while ours was 24 weeks. Secondly, the control group used in the study is different from ours, which may affect the results of the study. Finally, the daily activity of the patients in the control group could not be quantified. After the inclusion of the patients, we could only see those with significantly increased or decreased daily activity, and carried out elimination management, but we could not make quantitative comparison with the patients in the intervention group.

Despite its limitations, the results of this trial are expected to provide evidence for the efficacy, safety and economic benefits of Baduanjin in the treatment of chronic low back pain. To provide medical staff, medical staff and patients with long-term exercise therapy plan recommendations.

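### The planned significance test of Baduanjin-associated adverse events has no useful null hypothesis, because the control arm does no Baduanjin; report these events in the exercise arm only, with an exact confidence interval

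*Protocol article*

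**What the plan says.** The last sentence of the first paragraph of Statistics (2.21) sets two tested safety endpoints: "the total adverse event rate and adverse event rate associated with Baduanjin were tested by Pearson" chi-squared or Fisher's exact test. It does not name the groups compared. The Abstract, however, lists safety among the outcomes to be compared.

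Exposure differs completely between the arms. Under Research design (2.2), "All the members of the intervention group received Baduanjin training 3 times a week for 24 weeks", whereas "All cases in the control group did not receive any exercise training for 24 weeks". Control group (2.13) repeats the second point: "Participants in the control group did not receive any special sports training".

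Assess safety (2.18) says "The incidence of adverse events will be calculated" and treats intervention-related events as a class of their own: "Adverse events associated with the intervention will be monitored and appropriately addressed". Nothing in the article restricts the Baduanjin-associated endpoint to the exercise arm. The Discussion (3) lists as a strength that "safety index evaluation is included for the first time to verify the safety of Baduanjin training".

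**The concern.** A two-sample test of proportions is useful when both arms could produce the event and the question is whether they do so at the same rate. An event attributed to Baduanjin needs exposure to Baduanjin, which the control arm does not have by design. The null hypothesis of equal rates therefore reduces to a related-event rate of zero under Baduanjin, and one event refutes that without any test.

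The p-value can mislead in either direction. A non-significant result can sit beside a related-event rate that clinicians would want to know about. A significant one would be a product of attribution, since only one arm can supply such events and Blinding (2.9) says that participants and physicians are not blinded. Safety is among the stated Objectives (2.1), and the Introduction faults earlier trials for lacking safety observation, so this part of the results is likely to be read closely.

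**Working it through.** **Inputs.** Arm size: "the sample size of this study is 45 patients per group" (Sample size calculation, 2.7). Control exposure to Baduanjin: none (2.2, 2.13). Loss to follow-up of up to 20% (2.7) leaves 45 × 0.80 = 36 per arm. The article gives neither the sidedness nor a separate significance level for the safety tests, so two-sided 0.05 is assumed. It gives no expected related-event rate, so a range is shown.

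**The plan's own figure.** There is none for safety. The arm size reproduces from the VAS inputs in 2.7:
- difference 3.70 − 2.37 = 1.33
- pooled SD √((1.7² + 1.39²)/2) = 1.553
- n = 2 × (1.960 + 1.645)² × (1.553/1.33)² = 35.4, so 36 per arm
- 36/0.80 = 45

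**Test against zero.** With k events in 45 exercise patients and 0 in 45 controls:
- two-sided Fisher p = 2 × C(45,k)/C(90,k), for k ≥ 1. For k = 5: 2 × 1,221,759/43,949,268 = 0.056.
- uncorrected Pearson statistic = 90k/(90 − k) on 1 degree of freedom. For k = 4: 360/86 = 4.19, p = 0.041.
- exact (Clopper-Pearson) 95% limits for the exercise arm: the 2.5% point of Beta(k, 46 − k) and the 97.5% point of Beta(k + 1, 45 − k).

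| Related events, exercise arm | Rate | Exact 95% CI | Fisher p | Pearson p |
|---|---|---|---|---|
| 1/45 | 2.2% | 0.1 to 11.8% | 1.00 | 0.31 |
| 3/45 | 6.7% | 1.4 to 18.3% | 0.24 | 0.078 |
| 4/45 | 8.9% | 2.5 to 21.2% | 0.12 | 0.041 |
| 5/45 | 11.1% | 3.7 to 24.1% | 0.056 | 0.021 |
| 6/45 | 13.3% | 5.1 to 26.8% | 0.026 | 0.011 |

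Up to five related events are not significant by Fisher. At four or five events the two named tests disagree, and the article gives no rule for choosing between them.

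**Chance of significance.** Fisher needs six or more events. The binomial probability of reaching that number is:

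| Assumed true related rate | 45 per arm | 36 per arm |
|---|---|---|
| 5% | 2.4% | 0.8% |
| 10% | 29% | 15% |
| 15% | 69% | 46% |
| 20% | 91% | 75% |

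So with a true related rate of 10%, the test would be non-significant about 71% of the time at full arm size.

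**The case against.** Several points on the other side have force.

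- **The comparison between arms is inferred.** The safety sentence names no groups, although the sentence before it does. The inference is still strong: the tests named compare groups, there are only two arms, and the Abstract has safety compared.
- **The control count is not zero by definition.** The article does not say what makes an event associated with Baduanjin or who decides, and evaluators are blinded. The Introduction calls Baduanjin widely used in China, and the Discussion admits that control activity could not be quantified. A control patient could practise it, or have an event classed that way. Zero is what the design leads one to expect, not a certainty. A stray control event would come from contamination or misattribution, so it would not rescue the test.
- **Safety is not left unexamined.** A reader might infer that the safety analysis as a whole is uninformative. It is not. The total adverse event comparison is sound, and section 2.18 provides for documenting every event, calculating incidence, and checking vital signs, blood tests and neurological status. Both arms are assessed on a common schedule (Study schedule, 2.11), with adverse events checked at each examination.
- **The harm is a risk, not a stated intention.** A reader might infer that a non-significant p-value will be reported as proof of safety. No section says so, and the Discussion sentence describes the inclusion of a safety evaluation rather than a decision rule.

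These points limit the criticism to one of the two tests. They do not give that test a useful null hypothesis.

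**Conclusion.** The test of Baduanjin-associated events is a poorly chosen analysis that the article itself states, so this is not a detail left to an unseen analysis plan. It tests a null hypothesis that one event refutes, and it can return a non-significant result at an observed related rate of 11.1% (exact 95% CI 3.7 to 24.1%, Fisher p = 0.056).

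This rests on four assumptions: the test is between arms, the control count is zero as the design implies, the level is two-sided 0.05, and 45 patients per arm are analysed.

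The limited precision of a 90-patient trial should not be counted as part of this fault. Even with no related events, the exact 95% upper limit is 1 − 0.025^(1/45) = 7.9%, or 1 − 0.025^(1/36) = 9.7% with 36 patients. Those bounds follow from the sample size and remain after the correction. The point affects a stated safety objective but not the primary VAS analysis or the sample size.

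**What to change.** In Statistics (2.21):
- Remove the significance test of Baduanjin-associated adverse events. Report the number and percentage of patients with such events in the Baduanjin arm only, with an exact 95% CI.
- Keep the between-arm comparison of all adverse events regardless of attribution, and present it as a risk difference with its CI.

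In the Discussion (3), describe the safety aim as estimating the rate of adverse events rather than verifying safety.

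The cost is a change of wording and a more modest safety claim. No additional patients or data are needed.

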### Inclusion criteria

2.3

1.Male and female subjects aged 19 to 70 years;2.Pain that lasts at least 3 months;3.At the time of inclusion, pain and discomfort were over 40 mm on the 100 mm Visual Analog Scale (VAS);^[30]^4.Normal intelligence, able to communicate and communicate, able to complete the basic movements of Baduanjin;5.Voluntarily provide written informed consent and are willing to follow instructions related to the trial.

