### Outcome indicators

2.16

#### 
Primary endpoint

2.16.1

The main outcome of our study will be the change in VAS score of pain from baseline to the completion of the intervention (week 24).^[30]^ Patients will quantify pain intensity by marking the most relevant points anchored by 2 descriptors on a 100 mm horizontal line: 100 for ”most imaginable pain” and 0 for ”no pain”.

#### 
Secondary ending

2.16.2

Pain-related disability index is used to measure general disability related to pain.

The Pain Disability Index is a widely used and researched tool for measuring pain-related disability, especially in chronic low back pain, fibromyalgia, cancer, or chronic generalized pain.^[33]^ Pain Disability Index is mainly composed of 7 projects, including family responsibilities, entertainment, social activities, occupation, sexual behavior, self-care, and life support activities. Each item is evaluated using a numerical score scale of 0 to 10, where 0 means no disability, 10 means the highest disability, and the total score is 70 points. The higher the score, the more the pain interferes with daily activities. Pain Disability Index is easy to understand and is an effective and reliable tool.

The Quebec back pain disability scale is used to measure disability related to specific back pain.^[34]^

The Quebec back pain disability scale is mainly used to assess the difficulty of various daily activities patients with low back pain. These activities are mainly divided into 6 areas, across a total of 20 questions: bed rest (question 1–3), sitting (question 4–6), walking (question 7–9), exercise (question 10–12), bending over (question 13–16) and carrying heavy objects (questions 17–20). Each question has 6 options, with a score of 0 to 5. A score of 0 means no difficulty, a score of 5 means unable to complete, and a higher score means more severe dysfunction. The total score is 100 points.

Measure the health-related quality of life through the SF-36 Health Survey.^[35]^

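### The primary mixed model has a random intercept only, so the standard error of the week-24 change in VAS can be too small or too large

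*Protocol article*

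**What the plan says.** Section 2.21, in the paragraph on the primary analysis of treatment efficacy, specifies "a linear mixed model (random intercept and fixed coefficient", "which includes treatment, time, and time interaction". It takes the effect from the interaction: "The treatment coefficient of time interaction provides an estimate of the effect of Baduanjin intervention". It then adds: "The magnitude of the treatment effect will be calculated for each follow-up time point". No random slope, residual covariance structure or robust standard error is named, and time is not said to be categorical or continuous.

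Three other statements bear on the point:

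- Visits (section 2.2): "Primary and secondary outcomes will be measured at baseline, 8, 16 and 24 weeks after intervention, and the next 4 weeks", that is, weeks 0, 8, 16, 24 and 28.
- Primary endpoint (section 2.16.1): "the change in VAS score of pain from baseline to the completion of the intervention (week 24").
- Entry (section 2.3): "pain and discomfort were over 40 mm on the 100 mm Visual Analog Scale (VAS").

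Section 2.21 also plans a Student's t or Mann-Whitney test, which "will be used to analyze the difference between the intervention group and the control group at each time period".

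**The concern.** With independent, equal-variance residuals, a random intercept gives compound symmetry: one variance for all visits and one correlation for all pairs. Two features of this design make that doubtful.

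- Weeks 0 and 24 are treated as being as closely correlated as weeks 24 and 28, although the gaps are 24 and 4 weeks. Repeated scores commonly become less alike as the gap grows.
- Baseline VAS is cut off at 40 mm and later scores are not, so the baseline spread is probably narrower.

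The primary endpoint spans weeks 0 to 24, but the model takes its variance from one within-patient mean square pooled over all five visits. If correlation decays, that pooled figure is too small for so long a gap. If the baseline spread is narrower, it is too large. At stake are the confidence interval and p-value of the trial's main result.

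**Working it through.** **Figures in the plan.** The protocol gives no variance, correlation or error rate for the mixed model, so there is no figure of that kind to reproduce. Its sample size does reproduce. The pooled SD is √((1.7² + 1.39²)/2) = 1.553 and the difference is 3.70 − 2.37 = 1.33. Then n = 2(1.960 + 1.645)² × 1.553²/1.33² = 35.4, rounded up to 36, and 36/0.8 = 45 per group. This calculation does not involve the mixed-model covariance.

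**Setting for the check.** Five visits at weeks 0, 8, 16, 24 and 28; categorical time; baseline as an outcome row; complete data; equal groups. V is the true covariance matrix of one patient's five scores, with later-visit variance set to 1. Every V below is an assumption.

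**Formulas.**

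- Within-patient mean square that the model estimates: s² = (mean of the 5 variances) − (mean of the 10 covariances).
- Model variance of one patient's change to week 24: 2s².
- True variance of that change: V(0,0) + V(24,24) − 2V(0,24).
- SE ratio: R = √(model variance / true variance). The number per group cancels.
- Actual two-sided error at nominal 5%: 2(1 − Φ(1.96R)).

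**Worked example 1: pure decay, correlation 0.7 per 8 weeks.** The ten correlations are 0.700 (three times), 0.490 (twice), 0.343, 0.287, 0.410, 0.586 and 0.837, with mean 0.554. So s² = 1 − 0.554 = 0.446 and the model variance is 0.891. The true variance is 2(1 − 0.343) = 1.314. R = √(0.891/1.314) = 0.824, and the error is 10.6%.

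**Worked example 2: narrower baseline only, SD 0.6 of later SDs, constant correlation 0.5.** The mean variance is (0.36 + 4)/5 = 0.872 and the mean covariance is (4 × 0.30 + 6 × 0.50)/10 = 0.420. So s² = 0.452 and the model variance is 0.904. The true variance is 1 + 0.36 − 2 × 0.30 = 0.760. R = 1.091, and the error is 3.3%.

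**Worked example 3: mixed pattern.** Take 40% stable patient variance, 30% decaying at 0.7 per 8 weeks and 30% visit-to-visit noise. Then s² = 0.3 × (1 − 0.554) + 0.3 = 0.434 and the model variance is 0.867. The true variance is 2(0.3 × 0.657 + 0.3) = 0.994. R = 0.934, and the error is 6.7%. The stable part cancels from both variances; it is the noise that dilutes the effect of the decay.

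| Assumed covariance | R | Actual error |
|---|---|---|
| Equal variance, constant correlation | 1.00 | 5.0% |
| Narrower baseline only (SD 0.6), correlation 0.5 / 0.7 | 1.09 / 1.05 | 3.3 / 4.1% |
| Mixed pattern, equal SDs | 0.93 | 6.7% |
| Mixed pattern, baseline SD 0.8 / 0.7 / 0.6 | 0.98 / 1.00 / 1.02 | 5.4 / 4.9 / 4.6% |
| Pure decay 0.7, baseline SD 0.6 | 0.91 | 7.5% |
| Pure decay 0.3 / 0.5 per 8 weeks | 0.91 / 0.87 | 7.3 / 9.0% |
| Pure decay 0.6 / 0.7 / 0.8 / 0.9 per 8 weeks | 0.84 / 0.82 / 0.81 / 0.79 | 9.8 / 10.6 / 11.4 / 12.2% |

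The extremes among all patterns tried were 2.6% (constant correlation 0.3, later SD twice the baseline SD) and 13.8% (correlation 0.3 with baseline, 0.8 among later visits).

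**Simulation check.** With 45 per group and 20,000 null trials, the random-intercept test rejected in 10.6% (pure decay 0.7), 6.8% (mixed, equal SDs), 4.8% (mixed, baseline SD 0.7) and 3.2% (baseline SD 0.6, correlation 0.5). A test using the observed variance of the week-24 change stayed at 4.9-5.0% in all four. With complete data, an unstructured covariance gives that same variance for this contrast.

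**The case against.** **A condensed article.** Residual structure, degrees of freedom and convergence rules are commonly left to an analysis plan, and SPSS MIXED can combine a random intercept with a structured residual. This stands in part: compound symmetry is the plain reading of the text, not a certainty. But the article does not merely stay silent. It names the random part of the model that it labels primary, and that choice can be judged.

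**Opposing mechanisms.** Decay makes the standard error too small, and a narrower baseline makes it too large. With the mixed pattern and a baseline SD of 0.6-0.8, the error is 4.6-5.4%, close to nominal. This stands. A reader might infer from the pure-decay rows that the false-positive rate is roughly doubled. The documents do not support that, because they give no covariance with which to choose among the rows.

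**Dependence on the contrast.** For the plain group difference at week 24 from the same model, the error is 5.0% under any decay with equal variances. This stands, and the article does not say whether baseline is an outcome row. But the endpoint is defined as change from baseline, and the effect is read from the interaction, so the change contrast is the natural reading.

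**A linear slope.** The singular interaction coefficient might suggest that time enters as one straight line. The text does not support that: section 2.21 promises an effect at each follow-up time point, and the Discussion also speaks of the effect at each recorded time point. Both point to categorical time.

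**The per-visit tests.** The planned t or Mann-Whitney tests do not depend on this covariance. That is true, but they do not repair the model that carries the primary label.

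**Conclusion.** The point holds as a weakness in a stated method. The random-intercept model imposes a covariance pattern that the visit spacing and the entry cut-off make doubtful, and the standard error of the primary contrast can be wrong in a direction that cannot be known in advance. At nominal 5%, the actual error is about 3-4% with a narrower baseline alone, about 5-7% under mixed patterns, and about 10-12% under pure decay at 0.6-0.9 per 8 weeks. These figures assume independent equal-variance residuals in the fitted model, categorical time, baseline as an outcome row, complete data, and covariances that the protocol does not supply. Inflation of the error rate is possible but not established. It is worth changing because a model that does not need the assumption is available in the planned software.

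**What to change.** In section 2.21, or in the analysis plan before unblinding, state that:

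- visit is categorical (weeks 0, 8, 16, 24, 28), which also removes any doubt about how time enters;
- the covariance across visits is unstructured (SPSS MIXED, REPEATED with COVTYPE(UN)), replacing the random intercept, with Satterthwaite degrees of freedom;
- if the model does not converge, a named simpler structure is used, for example heterogeneous Toeplitz or heterogeneous AR(1);
- the primary effect is the treatment-by-visit contrast for change from baseline to week 24.

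The cost is wording only. The statistical price is up to 5 × 6/2 = 15 covariance parameters instead of 2, which 90 patients can support. No visit, measurement or sample size changes.
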